## Abstract

**Background:**

Post thrombotic syndrome (PTS) is a burdensome and costly complication of deep venous thrombosis (DVT) that develops in 20–40% of patients within 1–2 years after symptomatic DVT. Affected patients have chronic leg pain and swelling and may develop ulcers. Venous valve disruption from the thrombus itself or thrombus-associated mediators of inflammation is considered to be a key initiating event for the development of venous hypertension that often underlies PTS. As existing treatments for PTS are extremely limited, strategies that focus on preventing the development of PTS in patients with DVT are more likely to be effective and cost-effective in reducing its burden. Elastic compression stockings (ECS) could be helpful in preventing PTS; however, data on their effectiveness are scarce and conflicting.

**Methods/Design:**

The SOX Trial is a randomized, allocation concealed, double-blind multicenter clinical trial. The objective of the study is to evaluate ECS to prevent PTS. A total of 800 patients with proximal DVT will be randomized to one of 2 treatment groups: ECS or placebo (inactive) stockings worn on the DVT-affected leg daily for 2 years. The primary outcome is the incidence of PTS during follow-up. Secondary outcomes are severity of PTS, venous thromboembolism (VTE) recurrence, death from VTE, quality of life and cost-effectiveness. Outcomes will be evaluated during 6 clinic visits and 2 telephone follow ups. At baseline, 1 and 6 months, blood samples will be obtained to evaluate the role of inflammatory mediators and genetic markers of thrombophilia in the development of PTS (Bio-SOX substudy).

**Discussion:**

The SOX Trial will be the largest study and the first with a placebo control to evaluate the effectiveness of ECS to prevent PTS. It is designed to provide definitive data on the effects of ECS on the occurrence and severity of PTS, as well as DVT recurrence, cost-effectiveness and quality of life. This study will also prospectively evaluate the predictive role of biomarkers that are reflective of putative underlying pathophysiological mechanisms in the development of clinical PTS. As such, our results will impact directly on the care of patients with DVT.

**Trial Registration:**

NCT00143598 and ISRCTN71334751

## Background

### The post thrombotic syndrome

The post thrombotic syndrome (PTS) (sometimes called 'post-phlebitic syndrome') is a chronic condition that develops in 20–40% of patients within 1–2 years after symptomatic deep venous thrombosis (DVT). A severe form, which can include venous ulcers, affects 1/4 to 1/3 of patients with PTS [1]. In contrast to research gains in the areas of diagnosis, prevention and treatment of acute venous thromboembolism (VTE), PTS has been understudied and as a result, treatment options are limited.

Patients with PTS experience pain, heaviness, swelling, or other symptoms in the affected limb, which are typically aggravated by standing or walking and improve with rest and recumbency. Edema, venous ectasia, hyperpigmentation, eczema, and varicose collateral veins may be apparent. In severe cases, ulceration can occur [2].

Since PTS is a direct consequence of DVT, its prevalence is influenced by the incidence of DVT. Despite advances in VTE prevention and treatment, the annual incidence of VTE has not decreased over time, and remains at 1.0–1.6 per 1000 persons per year, with a per-person lifetime incidence of 2–5% [3,4]. Because of its prevalence and chronicity, PTS is expensive, both in terms of direct medical costs and indirect costs such as loss of productivity and thus it is burdensome to patients and society [5].

### Risk factors for the development of PTS

While hereditary and acquired risk factors that predispose to the development of VTE are widely known [6], factors that influence the development of PTS after DVT have not been well elucidated. The only clearly identified clinical risk factor for PTS is recurrent, ipsilateral DVT [7,8]. The site (proximal vs. distal), size and occlusiveness of the initial DVT and the intensity (i.e. target INR) of long term anticoagulation for DVT do not appear to reliably predict PTS [1,7-10]. It is not clear why some patients develop PTS while others recover from their DVT. As a result, physicians are unable to provide their DVT patients with reliable, individualized prognostic information.

### Potential role of inflammation, d-Dimer and thrombophilia in the post-thrombotic syndrome

While the pathophysiology of PTS is incompletely understood, it is likely that the acute thrombus itself, associated mediators of inflammation, and the process of vein recanalization in the weeks following DVT induce damage to venous valves, leading to valvular incompetence (reflux). Valvular incompetence and/or persistent venous obstruction by thrombus cause venous hypertension, which promotes capillary leakage of plasma proteins, erythrocytes and leukocytes and the development of venous ectasia and varicosities. The result is edema, tissue hypoxia, and ultimately, in some cases, skin ulceration [11-14].

Inflammation and thrombosis are closely interrelated [15-17]. It has been appreciated over the last few years that arterial atherothrombosis is, at least in part, an inflammatory disease, and that elevations in markers of inflammation, such as C-reactive protein (CRP), increase the risk of future clinical cardiovascular events [18]. Clinically, patients with DVT exhibit cardinal signs of inflammation such as redness, warmth, swelling, pain and fever. Several clinical studies have examined the association between levels of inflammatory markers and venous thrombosis, and found that a two- to six-fold increase in the risk of DVT associated with elevations in plasma levels of CRP, interleukin (IL)-6, IL-8, monocyte chemotactic protein (MCP)-1 or tumor necrosis factor (TNF)-alpha [19]. A recent paper showed that CRP is elevated in patients with acute DVT (median 37.5 mg/L) compared with controls (5.0 pg/L), and that levels decline during the first 5 days of DVT treatment. Similar trends were noted for IL-6 [20], leading the authors to conclude that the thrombotic process produces a systemic inflammatory response and to speculate whether the observed decrease in levels was partly caused by treatment with heparin, which is known to have anti-inflammatory properties distinct from its anticoagulant properties [21]. Whether levels of markers of inflammation are predictive of PTS has not previously been examined.

D-dimer is a degradation product of cross-linked fibrin that reflects fibrinolysis and is an indirect marker of coagulation activation. Recent work performed by our group and by others suggests that D-dimer levels appear to be a significant predictor of first VTE [22] and of recurrent VTE [23-28], whether measured during or after anticoagulation. Independent of VTE recurrence, persistent coagulation activation, as reflected by elevated D-dimer levels, may also predict a higher risk of developing PTS after DVT [29].

Thrombophilia refers to an inherited or acquired predisposition to VTE. Over 10% of the general population is affected by one or more identifiable inherited thrombophilias which have been shown to underlie at least 1/3 of cases of VTE [30]. The most common inherited thrombophilias are the single nucleotide polymorphisms Factor V Leiden, which renders coagulation factor V resistant to the anticoagulant effects of activated protein C [31], and Prothrombin G20210A, which leads to elevated plasma prothrombin levels [32,33]. Recent studies have also established that elevation of Factor VIII level is an inherited risk factor both for first and for recurrent VTE [34-36], independent of age, sex, Factor V Leiden, Prothrombin G20210A or markers of acute phase activation such as CRP [35,37,38].

While results of a few studies to date suggest that thrombophilia does not increase the risk of developing PTS [7,8,10], not all thrombophilias have been examined and interactions among disorders have not been studied. Further investigation of the potential link between thrombophilia and PTS is warranted.

### Management of PTS

PTS could be averted by primary prevention of the initial DVT with the judicious use of thromboprophylaxis [39], and by preventing recurrent ipsilateral DVT by prescribing adequate anticoagulation for the initial DVT [40]. However, at least 1/2 of all cases of DVT occur unpredictably, hence are not preventable [41,42]. There is no definitive evidence that using thrombolysis to treat DVT reduces the incidence of PTS [43]. The treatment of established PTS is limited and frustrating for patients. Severe PTS can be managed with long-term use of an intermittent compression extremity pump [44,45]. Management of venous ulcers is labor intensive and protracted, and involves compression therapy, leg elevation, topical dressings, and sometimes surgery [2,46]. Ulcers are often recalcitrant to treatment, and tend to recur [47].

A significant reduction in the overall burden of PTS is unlikely to be achieved by attempts to prevent the initial DVT or by treatment of established PTS. Rather, strategies that focus on preventing the development of PTS in patients with DVT are more likely to be effective and cost-effective in reducing the patient and societal impact of PTS.

### Elastic compression stockings for the prevention of PTS

Graduated elastic compression stockings (ECS) work by providing graded compression to the leg that is highest at the ankle, which assists the calf muscle pump, reduces venous hypertension and valvular reflux, and consequently reduces edema, improves tissue microcirculation, and prevents skin breakdown [48,49]. Both knee-length and thigh-length stockings appear to have equal physiological effects, but knee-length ECS are easier to apply and are more comfortable [50]. The effectiveness of daily use of ECS to prevent PTS is supported by two studies [8,51] but challenged by another [52]. All three studies have limitations that could affect their validity and generalizability. The first trial, Brandjes' study of 194 patients with symptomatic proximal DVT, provides evidence supporting the effectiveness of ECS. Patients were randomized to daily use of custom-made, knee-length ECS applied within 2–3 weeks of diagnosis for at least 2 years (class II compression, i.e. 30–40 mm Hg pressure at the ankle), or no stocking. Use of ECS resulted in a 50% reduction in the incidence of PTS, diagnosed using a modification of Villalta's clinical PTS scale [53], or an absolute decrease from 47% to 20% of mild/moderate PTS and from 23% to 11% of severe PTS [51]. In contrast, a randomized trial conducted by Ginsberg suggested that ECS were not of benefit in preventing PTS [52]. A strength of Ginsberg's study was the use of a control comparison group that wore sham stockings (i.e. stockings that were 1–2 sizes too big to be effective). However, because of the small number of patients with PTS, benefit or harm of up to 30% could not be definitively excluded. Recently, Prandoni published the results of a trial performed at a single center in Italy to evaluate the effectiveness of ECS to prevent PTS [8]. Among 180 patients with proximal DVT, those randomized to wear daily ECS had a 50% reduction in the rate of PTS after a 2 year period, compared with controls. This study, like Brandjes', lacked a placebo control, an important limitation due to the subjective nature of many of the components of the standardized scale that was used to diagnose PTS [54]. As the Prandoni study was the first, single positive study of "off-the-rack" elastic compression stockings, it requires replication. Also, as the study was conducted entirely at a single center in Italy, further evaluation of the generalizability of this data to North American clinical practice in a multi-center study is needed.

In light of the above, we believe that a large scale, randomized placebo-controlled trial of ECS to prevent PTS is needed to provide definitive evidence of effectiveness, or lack of effectiveness, of ECS. This will allow physicians to make informed, evidence-based decisions regarding their use in DVT patients. Furthermore, such a trial will permit prospective evaluation of the predictive role of markers of inflammation, d-Dimer and thrombophilia in PTS.

## Methods/Design

The SOX Trial is a Canadian, multicenter, randomized double-blind controlled trial in patients with a first episode of proximal DVT.

### Aims of the study

The primary aim of the study is to evaluate whether graduated elastic compression stockings compared to inactive (placebo) stockings, worn daily for 2 years after DVT is diagnosed, decrease the incidence of PTS.

Secondary aims are 1) to evaluate whether active compared with inactive stockings reduce the severity of PTS, 2) to compare mean quality of life (QoL) scores during follow-up in the active intervention vs. control groups, 3) to describe the rates of recurrent DVT, death from VTE, venous ulcers, and major bleeding during the 2-year follow-up in the active intervention vs. control groups, 4) to evaluate the cost-effectiveness of ECS for the prevention of PTS, and 5) to determine whether markers of inflammation, D-dimer and thrombophilia influence the development and severity of PTS (Bio-SOX biomarker substudy).

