#### Current trial design

The study is a randomized, allocation concealed, double-blind multicenter clinical trial with an intervention allocation ratio of 1:1 (figure 1 summarizes the study design). Once a patient is deemed eligible and consents to the study, the research nurse at each site logs onto a web-based interface which allocates the patient to one of 2 treatment groups: active stockings or inactive (placebo) stockings. Treatment group is assigned randomly using permuted blocks of randomly varying sizes at each study site to maintain close balance of the numbers in each treatment group, at any time during the trial, and to ensure allocation concealment. The active stockings intervention consists of knee-length, 30–40 mm Hg (Class II), graduated ECS worn on the DVT-affected leg daily, applied upon waking and removed upon retiring, beginning as early as possible within 14 days after DVT diagnosis and continued for 2 years. The inactive stockings intervention (the control intervention) consists of knee-length, inactive stocking (5 mm Hg compression at ankle; similar to store bought trouser sock), identical in appearance to the active stockings, worn on the DVT-affected leg daily, applied upon waking and removed upon retiring, beginning as early as possible within 14 days weeks after DVT diagnosis, and continued for 2 years. Active and inactive stockings are manufactured by SIGVARIS Corp.

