### Statistical analysis

An intention-to-treat analytical approach will be used for all outcomes. Descriptive statistics for baseline variables will be calculated to describe the baseline status of the treatment groups. For the primary outcome variable PTS, a logistic regression analysis initially adjusted only for center will be used to compare the incidence rates between the active vs. inactive stockings groups. In secondary analyses, other covariates that will be adjusted for are duration of anticoagulation with warfarin, recurrent ipsilateral DVT during follow-up, temporary use of active stockings, initial type and duration of heparin anticoagulation, co-morbid conditions that could lead to leg symptoms/signs and differences in pertinent baseline variables. The number needed to treat for benefit will be calculated. As an adjunct to the primary analysis, a secondary explanatory (per-protocol) analysis will be performed as well. Subgroup analyses by age, sex, level of compliance, duration of warfarin anticoagulation and recurrent VTE during study follow-up are also planned.

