For the secondary outcomes valvular reflux, recurrent VTE, death from VTE, venous ulcer, major bleeding, and severity of PTS, rates in the two intervention groups will be described, and between-group differences explored in similar regression procedures. For differences in mean quality of life scores between intervention groups, analysis of variance incorporating treatment and center will be used. A difference of 4–5 points between groups is considered to be clinically meaningful. Analysis of covariance with adjustment for age, sex and comorbidity will also be used to compare quality of life between groups. For the biomarker variables, univariate analysis will be used to determine the strength of association between each biomarker variable and the occurrence of PTS. For genetic markers, heterozygotes and homozygotes will be analyzed together, given the rarity of homozygotes. IgG, IgM and lupus anticoagulant results will be dichotomized as normal or abnormal. Factor VIII, D-dimer and markers of inflammation will be analyzed both as continuous data and as proportion of values exceeding the upper 90^th ^percentile. For binary and nominal data, the appropriate chi-square tests will be used to examine the respective crude associations, and for continuous variables, the unpaired 2-tailed t-test. To examine adjusted associations, multiple logistic regression analyses will be performed in which the dependent variable is the presence of PTS. The independent variables to be tested are markers of thrombophilia, D-dimer, and levels of CRP, IL-6, IL-8 and MCP-1. Other variables of interest (for interaction and/or confounding) are age, sex, ethnicity, comorbid illness, allocation to active ECS, type and duration of heparin and warfarin use, type of DVT (unprovoked vs. secondary; anatomic extent of DVT), and recurrent DVT during follow-up. The analyses will aim to (1) identify the strength of the association between relevant biomarkers, other relevant explanatory variables and PTS; and (2) explore relevant interactions. Similarly, multiple linear regression will be performed in which the dependent variable is the severity of PTS, as measured by the Villalta scale.

An interim analysis for efficacy will be performed when half of the subjects have completed 2 years of follow-up. The analysis plans call for a Lan-DeMets alpha spending approach with an O'Brien Fleming boundary [70].

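### The covariate list for the adjusted biomarker models omits center, which the plan includes in its randomised PTS and quality-of-life comparisons; adding it is a cheap safeguard against site confounding

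*Protocol article*

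**What the plan says.** Secondary aim 5 (Aims of the study) is "to determine whether markers of inflammation, D-dimer and thrombophilia influence the development and severity of PTS".

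The Statistical analysis section treats center differently in two groups of analyses.

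- **Arm comparisons.** PTS is compared by "a logistic regression analysis initially adjusted only for center". For quality of life, "analysis of variance incorporating treatment and center will be used". Allocation uses "permuted blocks of randomly varying sizes at each study site" (Current trial design).
- **Biomarker analyses.** First, "univariate analysis will be used to determine the strength of association between each biomarker variable and the occurrence of PTS". For categorical markers "the appropriate chi-square tests will be used to examine the respective crude associations", with t-tests for continuous ones. Multiple logistic regression for PTS follows. Its covariates are enumerated: "Other variables of interest (for interaction and/or confounding) are age, sex, ethnicity, comorbid illness, allocation to active ECS", and then "type and duration of heparin and warfarin use, type of DVT (unprovoked vs. secondary; anatomic extent of DVT), and recurrent DVT during follow-up". A linear regression on the Villalta score is to be done in the same manner. Center is not in the list, and no stratification or clustering by center is stated for any biomarker analysis.

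**The concern.** Randomisation within site already keeps center from systematically confounding the stocking comparison. Marker levels are not randomised, so that protection does not extend to them. Center is therefore named where confounding by site is not expected and is absent where it is possible.

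For center to bias a marker-PTS association it must relate to both. The protocol describes routes on each side.

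- **Outcome.** Site nurses record PTS symptoms and signs at the visits (Table 1), and six of the eleven Villalta items are rated by a clinician (Primary and secondary outcome measures). Rating habits can differ by site.
- **Case mix.** Sites may differ in the patients they enrol, beyond what the listed covariates capture.
- **Exposure, enrolment inflammation samples only.** Patients may enter up to 10 days after diagnosis. The Background reports that CRP falls over the first 5 days of treatment, with similar trends for IL-6. A site that enrols earlier would tend to record higher values. Time from diagnosis to blood draw is not a listed covariate.

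At stake is a marker reported as associated with PTS when no such relation exists within sites. The Discussion says the findings could lead to therapies aimed at candidate biomarkers.

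**Working it through.** **The plan's own figure.** The concern disputes no stated number, but the evaluable sample size is an input. For 30% vs 20%, two-sided α 0.05 and 80% power:

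n per arm = [1.96·√(2·0.25·0.75) + 0.842·√(0.30·0.70 + 0.20·0.80)]² / 0.10² = (1.200 + 0.512)² / 0.01 ≈ 293.2, so 294 per arm and 588 in total. This agrees with the stated 600 to within 3%. Then 600 / (1 − 0.25) = 800, as stated.

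**Inputs from the protocol.** 600 evaluable patients; PTS about 25% (the mean of 30% and 20%); two-sided 5% test.

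**Inputs that are assumptions.** The protocol gives no number of centers and no between-center variation. The number of centers, the share of marker variance between centers, the SD of center effects on the PTS logit, and the correlation between the two sets of center effects are all assumed. A logit SD of 0.5 puts 80% of centers between about 14% and 38% PTS: −1.15 ± 1.28 × 0.5 gives logits of −1.79 and −0.51.

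**Simulation.** Data were generated with no marker effect within center. PTS was regressed on the marker without center and then with center. One run used 3000 replicates per setting and a second used 600.

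| Centers | Marker variance between centers | Logit SD | Correlation | Rejection without center | Rejection with center | OR per SD, without / with |
|---|---|---|---|---|---|---|
| 20 | 10% | 0.5 | 0.5 | 12.7% (3000), 11.7% (600) | 5.5%, 5.0% | 1.07 / 1.00 |
| 10 | 10% | 0.5 | 0.5 | 14.5% (3000) | 5.4% | about 1.07 / 1.00 |
| 20 | 20% | 0.5 | 0.5 | 21.0% (600) | 4.8% | 1.11 / 1.00 |
| 20 | 10% | 0.5 | 1 | 33.3% (600) | 5.2% | 1.15 / 1.00 |
| 20 | 5% | 0.3 | 0.3 | 4.9% (3000) | 5.4% | – |
| 20 | 10% | 0.5 | 0 | 4.5% (600) | 3.8% | 1.00 / 1.00 |
| 20 | 5% | 0.3 | 0 | 4.5% (600) | 4.8% | 1.00 / 1.00 |
| 20 | 0% | 0.5 | 0 | 5.3% (600) | 6.8% | 1.00 / 1.00 |
| 20 | 10% | 0 | 0 | 4.8% (600) | 4.5% | 1.00 / 1.00 |

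With 20 centers and correlation 0, the 3000-replicate run gives 5.8% without center and 5.1% with it. The simulation error at 5% with 600 replicates is √(0.05·0.95/600) = 0.9 percentage points, so the rates from 3.8% to 6.8% lie within about two standard errors of 5%.

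**Check of the spurious OR.** To first order the false slope is correlation × √(variance share) × logit SD. For the first row this is 0.5 × √0.10 × 0.5 = 0.079, or OR 1.08. For correlation 1 it is 0.158, or OR 1.17. The simulated 1.07 and 1.15 are slightly lower, as expected, because averaging over centers attenuates a logistic slope.

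**The case against.** The case against is substantial, and much of it stands.

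- **Partial coverage already exists.** Heparin type and duration, comorbid illness, ethnicity, and DVT type and extent are all listed covariates. Heparin duration is a partial proxy for time since treatment began. PTS diagnosis rests on patient-reported pain and swelling, five Villalta items are patient-rated, and the Trial committees section describes blinded adjudication of outcome events. These measures narrow the routes. They do not close them, because the ratings originate at the site and the sampling interval itself is not a covariate.
- **The sampling window is narrow in reach.** A reader might infer that the 10-day window affects all markers. Table 1 does not support that: the enrolment sample is for inflammation markers, genetic markers are drawn at 1 month, and D-dimer and coagulation assays at 6 months. For those later samples only the rating and case-mix routes remain.
- **No contradiction.** Naming center in the arm comparisons follows from the site-blocked design, so leaving it out elsewhere is not an inconsistency. Nor are the biomarker analyses the only ones not protected by randomisation: the plan also has a per-protocol analysis and subgroups by compliance and by recurrent VTE during follow-up.
- **Crude tests.** The chi-square and t-tests are presented as crude associations, with adjusted models to follow. Requiring stratified versions would be a preference.
- **Standard errors.** A reader might infer that clustering alone makes the standard errors too small. At zero correlation the error rate is about 5% to 6%, which barely supports that.
- **Left to a fuller document.** This is an article, and a substudy model may be completed elsewhere. But the article does enumerate the confounders, so the omission is from a stated list.

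**Conclusion.** The point holds as a modest one. The enumerated covariates for the adjusted biomarker models, logistic for PTS and linear for the Villalta score, do not include center. These are non-randomised associations in which center could confound.

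The size cannot be computed from the protocol. Everything depends on whether center effects on the marker and on PTS are correlated. Under the assumed moderate correlation with 20 centers, the error rate is about 12% at a nominal 5%, with a spurious OR of about 1.07 per SD. The more extreme assumptions give 21% to 33% and ORs of 1.11 to 1.15. With uncorrelated or small center effects there is essentially no inflation. The simulated models contain no other covariates, so the center parameters should be read as what remains after the planned heparin, comorbidity and DVT adjustments.

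A reader might infer from the simulations that the biomarker findings will be materially biased. The documents do not support that: no between-center variation is reported, and the spurious ORs are small beside the OR of 2.0 in the power statement (whose scale is not given). The protocol also calls the inflammatory-marker analysis largely exploratory. This is a cheap improvement, not a flaw that threatens the trial.

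**What to change.** In the biomarker part of the Statistical analysis section, add center to the adjusted models:

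- **PTS:** center-stratified (conditional) logistic regression, or a random center intercept.
- **Villalta score:** a center term in the linear model.
- **Crude tests:** keep the chi-square and t-tests, labelled as descriptive.

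The cost is one line of wording and no new data. Under a stratified model, very small centers contribute little, and centers where no patient or every patient has PTS contribute nothing. A random intercept avoids that loss. It does assume that center effects are unrelated to the marker, so it may reduce the bias without removing it entirely; including the center mean of the marker as a covariate deals with this.
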